#### Concealment mechanism {16b}

The computer-generated allocation (indicating HACF or TACF arm) will be blindly placed in sealed envelopes by data managers. Envelopes will be labeled with the randomization number and stored in numeric order at the TU. After the participant provides informed consent, study counselors will select the next sealed envelope.

#### Implementation {16c}

The lead data analyst will run the complete computer-generated allocation list prior to the first enrolment (with 10–15% extra for anticipated losses to follow-up). For each participant, the study counselor will obtain informed consent prior to opening the sealed envelope with allocation number (indicating HACF or TACF arm).

### Assignment of interventions: blinding

#### Who will be blinded {17a}

This is an open-label trial in which both the participants and study staff will be aware of intervention arm after randomization. However, in an effort to reduce potential bias, principal investigators (PIs) and the co-investigators who will be analyzing results will be blinded as to intervention arm.

#### Procedure for unblinding if needed {17b}

N/A. The trial is open-label, and unblinding PIs and co-investigators will not be required.

## Data collection and management

### Plans for assessment and collection of outcomes {18a}

#### Objective 1: data collection

##### HACF arm

The NTEP HCW will visit participant homes at 6 and 12 months post-treatment completion to screen the index patient and HHCs for TB. All HH members who screen positive will have a spot sputum taken at home for microbiological testing at the TU.

##### TACF arm

The NTEP HCW will screen the index patient for TB via telephone calls at 6 and 12 months post-treatment completion; the index patient will also be asked about TB symptoms among HHCs. If TB is suspected among any HH members, a home visit will be conducted and spot sputum specimens will be collected for microbiological testing at the TU.

##### TB events

A two-part TB event questionnaire will be administered to individuals identified with new or recurrent TB during or between study time points. Part one of the questionnaire will be administered shortly after diagnosis and will include self-reported duration of TB symptoms. Part two will be administered at month 18 (“mop-up”) or at the end of that individual’s TB treatment, whichever is earlier.

##### “Mop-up” campaign

To determine total number of TB diagnoses across HHs in both arms, three strategies will be undertaken. First, all index patient names will be periodically cross-matched with the NTEP registry. Second, on all calls and at all home visits, participants will be asked if there were any TB diagnoses in the period since the last call/visit and when reported will be verified with the NTEP. Third, all HHs in both arms will have an 18-month home visit to screen all HH members for active TB and to survey them for history of TB. We will use the “mop-up” campaign data combined with the registry match data to account for all TB cases occurring during the study period. This will allow for more accurate comparisons between arms and to calculate proportion of overall recurrent and HH TB cases that were captured by our ACF strategies during the study period. In addition, we will compare timing of TB diagnoses between arms, as well as timing of TB detected by our ACF strategies vs. otherwise.

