#### Intervention description {11a}

In both arms, ACF will be conducted by existing NTEP HCWs at 6 and 12 months after the index patient completes TB treatment. Based on the WHO and Government of India guidelines, the HCW will screen for any symptom of TB, including cough for ≥ 2 weeks, hemoptysis, fever, night sweats, weight loss, or lymph node swelling to screen for extrapulmonary TB [24, 56]. For participants with any symptom of TB, sputum specimens will be collected outside the home in the open air. As per routine programmatic conditions, sputa will undergo Xpert testing (or available microbiologic testing) and results will be returned to the patient.

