**Index patients**						
Informed consent, enrolment and randomization	X					X
Socio-demographic and clinical questionnaires	X			X		X
Household geo-coding	X					X
Biomass fuel, smoking and alcohol exposure questionnaires	X			X		X
Point-of-care HbA1c test	X					X
Lung health assessments	X	X^a^	X^a^	X		X
Modified WHO survey for TB patient costs	X	X		X		X
TB symptom questionnaire	X	X	X	X	X	
TB event questionnaire		Any time TB case is identified				X

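### The month-18 reference symptom screen is assigned to the health-worker group that delivers both ACF strategies, so the share of cases captured by ACF is likely overstated

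*Protocol article*

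**What the plan says.** **Who screens at months 6 and 12.** Item {11a}, on the interventions, states: "In both arms, ACF will be conducted by existing NTEP HCWs at 6 and 12 months after the index patient completes TB treatment". In the home-based arm, the plan is: "The NTEP HCW will visit participant homes at 6 and 12 months post-treatment completion to screen the index patient and HHCs for TB". In the telephone arm the index patient is called and answers for the household: "the index patient will also be asked about TB symptoms among HHCs".

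**Who screens at month 18.** The Mop-up campaign section says "Third, all HHs in both arms will have an 18-month home visit to screen all HH members for active TB" but names no screener. Table 1 is the only place that does. Its "TB symptom questionnaire" row is ticked through month 18 for index patients and for household contacts. In both cases the administration tick is under NTEP HCW and the study-staff column is blank. Every other row with a month-18 tick is assigned to study staff: the socio-demographic, clinical and exposure questionnaires, lung assessments, cost survey, and contact consent.

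**The other two mop-up sources.** "First, all index patient names will be periodically cross-matched with the NTEP registry". Also, at calls and home visits, "participants will be asked if there were any TB diagnoses in the period since the last call/visit", with any report verified with the programme.

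**What the total is for.** Besides supporting the comparison between arms, the mop-up and registry data are to be used to "calculate proportion of overall recurrent and HH TB cases that were captured by our ACF strategies during the study period".

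**The concern.** The captured share has ACF detections in the numerator and all cases of the study period in the denominator. The denominator should come from a search that does not depend on the strategies being judged. Registry matching and self-report cannot show a case that nobody has yet diagnosed. Among the three sources, only the month-18 home screen can. Table 1 gives that screen to the cadre whose detection it is meant to check, using the same symptom questionnaire. A case overlooked earlier, for reasons of technique, rapport or the questions asked, is then more likely to be overlooked again.

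Three results are exposed: the captured proportion, the comparisons of diagnosis timing described with the mop-up, and the month 12–18 case totals. Those totals feed model calibration, because Model for recurrence and care-seeking uses the numbers diagnosed in each 6-month interval.

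The overlap also differs by arm. HACF shares worker group, questionnaire and home setting with the mop-up. TACF shares worker group and questionnaire, but screens by telephone with proxy report for contacts. The Exposures of interest section expects some TACF homes not to have been visited before the mop-up.

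**Working it through.** The protocol states no captured proportion, screen sensitivity or mop-up yield, so there is no figure of its own to reproduce. The check has two parts.

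**1. What each source can find**

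| Source | Who is covered | Finds undiagnosed cases? |
|---|---|---|
| Registry match | Index patients only | No |
| Self-reported diagnoses, verified | Participants asked at calls and visits | No |
| Month-18 home screen | All households, both arms | Yes |

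Contacts are 2152 of the planned 3228 participants (Sample size {14}), that is 2152/3228 = 67%, and the registry match as described does not reach them.

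**2. Effect on the captured share**

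For one arm, let c be the true share of cases found by ACF and p the share found by routine care. Then u = 1 − c − p is the share still undiagnosed before the mop-up, and m is the probability that the mop-up misses such a case. Cases counted are c + p + u(1 − m) = 1 − mu, so

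estimated share = c / (1 − mu).

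This exceeds c whenever m and u are both above zero. All values below are assumptions.

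*Equal true capture: c = 0.60, p = 0.20, u = 0.20 in both arms*

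- m = 0: 0.60/1 = 60.0%, no bias.
- m = 0.3: 0.60/(1 − 0.06) = 63.8%.
- m = 0.6: 0.60/(1 − 0.12) = 68.2%.
- m = 0.8: 0.60/(1 − 0.16) = 71.4%.

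With m = 0.3 in both arms, both shares are overstated by 3.8 points and there is no gap. With 0.6 in HACF and 0.3 in TACF the false gap is 68.2 − 63.8 = 4.4 points. With 0.8 and 0.3 it is 71.4 − 63.8 = 7.6 points.

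*HACF truly better: c = 0.60 versus 0.50, p = 0.20, so u = 0.20 versus 0.30; true difference 10 points*

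| m in HACF / TACF | HACF | TACF | Bias in difference (points) |
|---|---|---|---|
| 0.3 / 0.3 | 63.8% | 54.9% | −1.1 |
| 0.6 / 0.3 | 68.2% | 54.9% | +3.2 |
| 0.8 / 0.3 | 71.4% | 54.9% | +6.5 |
| 0.8 / 0.6 | 71.4% | 61.0% | +0.5 |

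The overstatement within each arm follows from any m above zero. The bias between arms depends on c and on mu in each arm. It can be positive, near zero or negative.

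**The case against.** Several points on the other side are sound and limit the claim.

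- **Same cadre, not same person.** A reader might infer that the worker who missed a case returns to the same home. The documents do not say so. Table 1 has one administration tick per row, not one per visit, and Study setting {9} says duties may be spread over several positions. Rural units have only two types of post, so a return by the same person is possible, but no more than that. Nor does any passage show that workers have a motive to hide earlier misses.
- **HACF favoured.** A reader might infer that the home arm's share is inflated more. That is plausible from the overlap, but proxy screening may leave more undiagnosed contacts in TACF, which works the other way, as the −1.1 row shows. It is also not safe to treat month 18 as the first meeting between TACF households and this cadre. Study setting {9} lists an early home visit with contact screening among existing duties, and Table 1 has an entry questionnaire under NTEP HCW for all index patients.
- **Other sources recover cases.** A missed case later diagnosed in care is counted whoever screens at month 18. Ignoring this inflates the effect: with p = 0, c = 0.60 and m = 0.6 the share would read 0.60/(1 − 0.24) = 78.9% instead of 68.2%. Study staff also see participants at month 18, and anyone who reports TB symptoms is referred under {11d}.
- **The primary outcome.** A reader might infer that the primary comparison is biased. A case first diagnosed at month 18 lies outside its 12-month window. The calibration counts from the month-6 and month-12 screens do not depend on the month-18 screener either.
- **Study staff are not a perfect reference.** They know the arm ({17a}), and misses caused by the symptom screen itself would remain.

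None of this makes the month-18 screen independent of the group being assessed.

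**Conclusion.** The point holds as a weakness in how the reference for the captured share is built. On the face of Table 1, the only systematic search for still-undiagnosed TB is done by the worker group whose detection it measures, and no other passage names a different screener. The captured share is therefore likely overstated. Assuming 60% true capture and 20% routine diagnosis, the overstatement is 3.8 points at a re-miss probability of 0.3 and 8.2 points at 0.6. A difference between arms is possible, 4.4 points in the 0.6 versus 0.3 illustration, but its sign and size rest on quantities the documents do not give. Some overstatement would remain under any imperfect screen. The shared cadre matters because it plausibly raises the re-miss probability, and that part is avoidable. The consequences reach the captured proportion, the timing comparisons and the month 12–18 calibration totals, and not the count of cases in the primary outcome.

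**What to change.** In Table 1, split the symptom-questionnaire rows so that the month-18 administration, for index patients and contacts in both arms, falls to study staff. Say the same in the Mop-up campaign section, and add that the screen is done without sight of the month-6 and month-12 screening results. Leave sputum collection and testing with the programme as now.

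The cost is a table edit, one sentence and a few more minutes per home, since study staff already carry out month-18 evaluations in both arms. There are two downsides. Misses caused by the shared symptom screen remain, so the captured share should still be described as an upper-leaning estimate. Also, the month-18 yield would no longer represent a programme-run third round, which Exploring variations on trial interventions mentions as a schedule to simulate.

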##### Exposures of interest

*Biomass fuel:* HH biomass fuel use will be assessed using self-reported questionnaires previously validated in our setting [60, 61].
*Smoking:* We will measure exposure to tobacco smoke, nicotine dependence based on the Fagerström Test for Nicotine Dependence, and heaviness of smoking among participants at entry [62].
*Alcohol:* We will measure alcohol use in adult (>= 18 years) participants at entry using the Alcohol Use Disorders Identification Test (AUDIT), which has been validated in India [63].
*Point-of-care HbA1c*: To identify diabetes, defined as HbA1c ≥6.5%, we will measure HbA1c among participants at entry using advanced fluorescent immunoassay technology (Standard F200, SD Biosensor, Republic of Korea). This point-of-care HbA1c test has been validated and approved by Indian regulatory authorities.
*HH socio-economic status:* Participants will describe their type of residence, the number of occupants, type of employment of employed individuals, and monthly HH income.

Visited HHs in both arms will be geocoded using android devises via Redcap during home visits. HHs not visited in the TACF arm will be geocoded during the “mop-up” visit. The residential location will be further characterized by collecting HH-level data such as: predominant housing type, sanitation and infrastructure, transportation access, and distance to closest TU.

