#### Which patients develop recurrent TB?

Identifying TB patients likely to develop recurrent disease could help target case-finding efforts and addressing modifiable risk factors could reduce the risk of recurrence. Prior studies have found an association between poor adherence to TB treatment and early recurrence suggestive of relapse [26, 27]. HIV is also a well-recognized risk factor for TB recurrence [10, 28, 29]. Diabetes is associated with a threefold higher risk of TB disease [30] and may be associated with recurrence as well [31, 32]. Alcohol consumption and exposure to tobacco smoke have both been shown to correlate with recurrent disease [28, 33–36]. Similarly, there is evidence that indoor air pollution increases risk of TB disease [37, 38]. Clinically, the pulmonary TB and lung impairment dynamic may be a vicious cycle; treated TB patients with pulmonary sequelae may be at higher risk of chronic lung diseases and subsequently recurrent TB [39]. Finally, socio-economic status and poverty are strongly linked to TB and likely impact risk of recurrence [40–42].

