#### Relevant concomitant care permitted or prohibited during the trial {11d}

Participants may not be enrolled in another clinical study involving follow-up time points that conflict with TB Aftermath. However, clinical care may be sought at the participant’s discretion during the study period. Participants who report symptoms suggestive of TB disease will be referred to the TU for evaluation. Likewise, asymptomatic HHCs who are identified as potentially eligible for TPT per NTEP guidelines but who have yet to access services will be referred for further evaluation. Index patients newly diagnosed with diabetes at entry, and any participant with lung impairment will also be referred for appropriate care.

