## Statistical methods

### Statistical methods for primary and secondary outcomes {20a}

The primary analysis will be intention-to-treat, which will include all enrolled participants who have completed TB treatment and their household contacts. The primary endpoint is rate of TB disease detected by study arm, which includes recurrent TB among index cases and new TB among HHCs including children. To assess non-inferiority of TACF, compared to HACF, we will estimate a 95% confidence interval around the difference between the observed TB cases diagnosed between arms and establish non-inferiority if the upper bound of this estimate is less than 3 per 100 person-years, the non-inferiority margin. We will analyze impact of key risk factors for TB disease (tobacco smoking, biomass fuel use, alcohol use, diabetes, respiratory impairment, low socioeconomic status, catastrophic costs) on the development of recurrent TB and new TB among HHCs. We will use mixed-effects Poisson regression with random effects for HH and fixed effects for individual level variables to measure the association of key risk factors with recurrent and new TB disease in the HH. For the secondary outcome, a logistic regression model with mixed effects, to account for HH level clustering, will be used to determine if HACF is independently associated with TPT initiation among children < 6 years of age.

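### Diabetes is defined only by one entry HbA1c of 6.5% or more, so as written known, treated diabetics below the cut-off count as non-diabetic in the risk-factor analyses

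*Protocol article*

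**What the plan says.** Under Exposures of interest, the article states: "To identify diabetes, defined as HbA1c ≥6.5%, we will measure HbA1c among participants at entry". In Table 1 the index-patient row "Point-of-care HbA1c test" is marked at entry only. Neither place counts a previous diagnosis or current glucose-lowering treatment, and no other definition of diabetes appears.

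The variable is then used. Statistical methods {20a} names the key risk factors as "tobacco smoking, biomass fuel use, alcohol use, diabetes, respiratory impairment, low socioeconomic status, catastrophic costs" and models them as follows: "We will use mixed-effects Poisson regression with random effects for HH and fixed effects for individual level variables". Exploring variations on trial interventions takes the frequency of risk factors and their relative risks from study data to simulate case finding aimed at high-risk patients. The Cost-effectiveness section also considers targeting by index-patient risk factors.

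Two other places bear on the point. Relevant concomitant care {11d} provides referral for "Index patients newly diagnosed with diabetes at entry". Table 1 also lists "Socio-demographic and clinical questionnaires" for index patients at entry, without showing what they ask.

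**The concern.** HbA1c reflects glycaemic control, and glucose-lowering treatment lowers it. A cut-off can detect diabetes in someone not yet diagnosed, but it cannot establish that a person already diagnosed and treated is free of the disease. Under the stated rule, a known diabetic treated to 6.2% joins the reference group, while an untreated patient at 6.6% is exposed. The error runs one way: it moves diabetics into the unexposed group.

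The referral provision speaks of new diagnoses, which has meaning only if existing diagnoses are recognised. The article draws that distinction for referral but does not carry it into the exposure definition.

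At stake are the diabetes rate ratio in the risk-factor model and, through the targeting simulations, both that ratio and the share of patients counted as diabetic.

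**Working it through.** The article states no figure for the association between diabetes and recurrence, so there is nothing to reproduce. What follows illustrates how large the effect of the definition could be. It is restricted to index patients, the group for whom Table 1 schedules the test.

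**Inputs from the article**
- Index patients: 1,076 (Sample size {14}).
- Relative risk: about 3, from "Diabetes is associated with a threefold higher risk of TB disease". This concerns TB disease. For recurrence the same section says only that an association is possible.

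**Inputs assumed, because the article gives none**
- D, the proportion of index patients with diabetes: 15% to 35%.
- f, the proportion of those below 6.5% on treatment: 10% to 40%.
- True rate ratio RR for recurrence: 3 (borrowed from the figure above) or 2.
- No non-diabetic reaches 6.5%.
- Controlled and uncontrolled diabetics carry the same risk (relaxed in the last step).

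**Formulas**
- Misclassified patients = 1,076 × D × f.
- Diabetic share of the reference group: c = D·f / (1 − D + D·f).
- Observed ratio = RR / [1 + c·(RR − 1)].

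**Results**

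| D | f | Misclassified | c | Observed, true RR 3 | Observed, true RR 2 |
|---|---|---|---|---|---|
| 15% | 10% | 16 | 0.015/0.865 = 1.7% | 2.90 | 1.97 |
| 25% | 30% | 81 | 0.075/0.825 = 9.1% | 2.54 | 1.83 |
| 35% | 40% | 151 | 0.14/0.79 = 17.7% | 2.21 | 1.70 |

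Middle row in full: 3 / (1 + 0.0909 × 2) = 3 / 1.182 = 2.54, and 2 / (1 + 0.0909 × 1) = 1.83.

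A second set of assumptions (D 10% to 30%, f 10% to 40%) gives the same picture: 11 to 129 patients misclassified, and a true ratio of 3 observed as 2.94 to 2.32.

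**Relaxing equal risk.** Suppose controlled diabetics have no excess risk. The HbA1c-only rule then gives 3 with no attenuation, but that 3 describes raised HbA1c at entry. A single variable for any diabetes would average the two kinds of patient: (1 − f) × 3 + f × 1, which is 2.8 at f = 10%, 2.4 at f = 30% and 2.2 at f = 40%. The two definitions therefore answer different questions. Only a variable that keeps the groups apart can show which case applies.

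**The case against.** The strongest reply is that the sentence sits under data collection, in an item about the HbA1c test, and that combining a test result with medical history is commonly left to a full protocol or analysis plan that is not shown. The entry questionnaire may record known diabetes, and the referral wording suggests that prior status is available. A reader might therefore infer too much in taking it as fact that treated diabetics will be analysed as non-diabetic. The documents do not settle what the final dataset will do. What remains is that the article does not leave the definition open: it defines diabetes by the cut-off alone, and anyone following it would misclassify these patients.

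The second reply is that raised HbA1c is a coherent exposure. The background gives addressing modifiable risk factors as one purpose, and if excess risk follows glycaemia, adding controlled patients would dilute the contrast. This is fair, and it is why the direction of any bias is conditional. It does not justify calling the variable diabetes without qualification.

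Third, the simulations would take prevalence and relative risk from the same definition, so they would be internally consistent as a model of targeting by that test. That also stands. It is tempting to add that a programme would select patients by diagnosis rather than by one HbA1c, but nothing in the article says so, and the point does not rest on it.

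**Conclusion.** The point holds as a mismatch between label and measurement in a stated definition. As written, previously diagnosed and treated patients below 6.5% fall into the reference group of the risk-factor model and outside the diabetic group in the targeting simulations.

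If controlled diabetics share the excess risk, the association is attenuated modestly: a true 3 becomes about 2.9 to 2.2, and a true 2 becomes 1.97 to 1.70. Diabetes would probably still appear as a risk factor. If they do not share it, there is no attenuation, but the estimate concerns hyperglycaemia at entry. Prevalence, the controlled fraction and the true ratio for recurrence are all assumptions, so the ranges show scale and do not predict a result.

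A reader might infer that the trial's main conclusions are at risk. They are not. Neither the non-inferiority comparison of the two case-finding arms nor the preventive-treatment outcome in children under 6 uses this variable, and sample size and allocation do not depend on it. Diabetes is one of seven listed risk factors.

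**What to change.** Under Exposures of interest, state that for the risk-factor analyses diabetes means entry HbA1c of 6.5% or more, or previously diagnosed diabetes, or current glucose-lowering treatment. Confirm that the entry clinical questionnaire records prior diagnosis and treatment, and add an item if it does not. Report as a secondary exposure either four groups (known and controlled, known and uncontrolled, newly detected, none) or HbA1c as a continuous variable. State which version supplies the prevalence and relative risk for the targeting simulations.

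This changes the analysis variable only and needs no new visit or test. For patients already enrolled, it depends on whether the history was recorded at entry. The price is some self-report error, since a few patients may report diabetes they do not have, and small numbers in some of the four groups.
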